This article thus describes the design of a large evaluation study on the Happiness Route. Based on the pilot studies and practical experiences, we hypothesize that emotional, social and psychological well-being of participants of the Happiness Route will increase in comparison to the traditional and commonly-used problem-based approach and health care will decrease. Furthermore, we will study whether the intervention decreases loneliness, depressive symptoms and consumption of care and whether it increases purpose in life, resilience, social participation and health-related quality. Last, we will examine if characteristics of both participants and counselors have moderating effects. As we handle strict inclusion and exclusion criteria and all counselors will receive the same thorough training, we do not expect moderating effects.

Existing studies on positive psychological interventions mostly had a limited amount of participants, were carried out in experimental settings, and with rather privileged groups with no psychosocial problems, such as students
[16]. The present study will belong to the 10% of the largest trials on positive psychological interventions
[27]. It is among the first to examine such an intervention in a practice-based research setting with several partners in the field of social work. Our study is also among the first to use an outreaching approach to target individuals with an accumulation of risk factors for low levels of well-being: lower socioeconomic status, social isolation, and health limitations
[1-5]. The study will thus provide new insights into the opportunities for mental health promotion in realistic settings.

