### Setting

The study will be carried out in the field of healthcare and social work in nine municipalities in the Netherlands by the University of Twente and Arcon, an organization in the welfare sector. The study is funded by ZonMw (the Netherlands Organisation for Health Research and Development) under the prevention program. A municipal officer will generally be the local project leader, but in some cases, the local project leader works in one of the participating institutions. The local project leader is responsible for the recruitment through intermediaries, the allocation of participants to counselors and for the final approval on spending the budget in the Happiness Route. Municipalities mostly provide financial support for the training of counselors, the appointment of the local project leader, as well as the budget for the Happiness Routes. In other cases, the project is financed by social funds.

The recruitment of participants will be carried out by intermediaries who work as professionals in local care and social work institutions. Examples of intermediary organizations and professions are home care, housing associations, after-care nurses, psychiatric nurses, religious institutions, well-being institutions and organizations for people with mental disabilities. Intermediaries are in direct contact with the target group in their daily work. They can suggest possible candidates to the local project leader, who informed the intermediaries about the study and the target group.

Counselors are experienced professionals, such as social workers, and in some cases experienced volunteers. They are responsible for the intake and the delivery of the experimental and control interventions. To avoid contamination between the experimental and the control conditions, counselors will only deliver interventions in one of these conditions. Both counselors providing the Happiness Route and counselors providing the control condition will receive suitable training.

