***Moderating measures***	
Demographics of participants	Gender, age, education, marital status, number of children, cultural background, income, employment status
Demographics of counselors	Gender, age, occupational level, financial situation, cultural background
Work characteristics of counselors	Work experience, work conditions
Work engagement	Utrechtse Bevlogenheid Schaal (UBES)
Work satisfaction	Vragenlijst Beleving en Beoordeling van de Arbeid (VBBA), General Work Satisfaction
Adherence of counselors	Online logs

Moreover, Vektis, the Dutch Information Centre for Care, will be asked to provide group statistics about the actual use of care. Vektis registers the use of healthcare by every Dutch citizen. Participants will be asked to provide their health insurance policy number and the name of their health insurance company on the informed consent, together with their permission to use the information as registered by Vektis. Vektis will execute the statistical analyses on possible differences in health care consumption before and after the intervention and to compare the use of care services between the experimental group and the control group.

Counselors also have to fill out a questionnaire before they start with their work for the study. Measures include demographic information, work experience, work conditions, work engagement (UBES; Utrechtse Bevlogenheidschaal)
[49] and work satisfaction
[50,51]. All counselors have to fill in online logs after each session. Happiness-counselors will give information about the recruitment, note the date of the session, give a short description of the session and describe their impression of the participant. They also have to answer questions about the motivation of the participant, the quality of their relation with the participant, the progress of the participant, the methods used in the session, and the current stage they are at. They also have room for further, free-text comments. The control counselors have to fill out similar, but somewhat shorter logs. After the second session, they have to fill out which changes were initiated, concerning the provision of care.

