#### Multivariate analyses

We will first do a missing data analysis for all participants on the second and third measurement point. A logistic regression analysis will be conducted with having complete data as the dependent variable, and demographic and psychosocial characteristics at baseline measurement as independent variables to assess non-random missings. We will use multiple imputations (five data sets) to replace missing values and carry out the analyses on the pooled data set. Hence, all participants who were randomized can be included in the statistical analyses. The results from this imputed intention-to-treat sample will be compared to the results of the observed data only.

We will use MANOVA analyses to assess the effectiveness of the intervention in reaching its primary and secondary outcomes. The measures at baseline, post-treatment, and follow-up are repeated measures and the experimental condition versus the control condition is the independent variable. In all analyses, we take into account that the observations are clustered as participants are ‘nested’ in each of the ten local institutions. Therefore, robust standard errors are computed using the first-order Taylor-series linearization method.

Standardized mean differences (Cohen's d) at post-intervention and follow-up are calculated as the difference between the means of the treatment and control condition divided by the standard error of the control condition. We expect a small to moderate effect size for the primary outcome (Cohen’s d= 0.35).

To answer the question on moderating participant factors, we will analyze the moderating effects of demographic characteristics (age, gender, and cultural background) on the effectiveness of the intervention. Following Kraemer et al.
[60], we will enter the change score of positive mental health at nine months minus baseline as a dependent variable in a linear regression model. The condition dummy (experimental versus control condition), the potential moderator, and their interaction are independent variables. When the interaction effect is significant, there is a differential effect of the intervention for this particular moderator. Analyses will be carried out for each of the three potential moderator variables separately.

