We do similar regression analyses to answer the question on moderating counselor factors. The potential moderators are the indices for work experience, work satisfaction, and adherence to the program as measured with the questionnaire for counselors and the logs of the counselors.

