### Power calculation and sample size

Based on a meta-analysis of previous studies in positive psychology, conducted with instruments that are similar to the MHC-SF
[27], we expect a small to medium effect size for the intervention Happiness Route (Cohen’s d = 0.35). A pilot study
[25] and experiences from previous practice showed that there are no negative effects on the well-being of participants. We therefore specified a one-tailed test with an alpha level of 0.05 under the assumption that the Happiness Route will be more effective than the Customized Care group, as the latter is not intended to improve positive mental health. This has also been shown in previous studies on positive psychological interventions
[27]. Given ethical considerations, Knottnerus and Bouter
[61] argued that one-sided testing is preferable under these circumstances. Power analysis with the program GPower with a power of 0.80 (1 – beta of 0.20), indicates that 102 participants are needed in each condition. We used a maximal drop-out rate of 20% which is a conservative estimate from previous experience. In everyday practice, the drop-out was about 10% of the more than 500 people who already participated in a Happiness Route. With a maximal drop-out of 20%, we need 128 participants in each condition, 256 in total.

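### Counselor adherence is tested as a treatment-effect moderator although it is recorded after randomization and refers to a different program in each arm

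*Protocol article*

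**What the plan says.** All references are to the protocol article.

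- **Model and decision rule (Multivariate analyses).** Participant moderators enter a linear regression of nine-month-minus-baseline change in positive mental health on condition, moderator and their interaction. The rule is: "When the interaction effect is significant, there is a differential effect of the intervention for this particular moderator". Counselor factors get similar regressions: "The potential moderators are the indices for work experience, work satisfaction, and adherence to the program".
- **Source of adherence (Moderating measures).** Counselors complete an online log for each participant after every home visit, and these logs can be used to measure adherence. Indices are described for work experience and work satisfaction, but none for adherence.
- **The logs (Data collection, after Table 1).** Happiness Route logs cover, among other things, the participant's motivation and progress, the methods used and the stage reached. For the other arm: "The control counselors have to fill out similar, but somewhat shorter logs". After the second session, control counselors also record the care changes initiated.
- **Counselors (Setting; Randomization).** To avoid contamination, "counselors will only deliver interventions in one of these conditions". The local project leader appoints the counselor once the allocation is known.
- **Expectation (Background; Discussion).** On moderation by participant and counselor characteristics, "we do not expect moderating effects". The Discussion says these assumptions will be tested.
- **Sample size (Power calculation and sample size).** The calculation covers only the main effect, at d = 0.35.

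**The concern.** Reading a condition-by-moderator interaction as effect modification requires a variable that allocation cannot have influenced and that means the same thing in both arms. Age, gender and cultural background meet this. Adherence to the assigned program meets neither condition: it does not exist until the program is under way, and the program differs by arm.

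If the score is also shaped by how the participant is doing, a stronger adherence-outcome association in one arm than in the other produces an interaction with no modification of the treatment effect behind it. Under the stated rule, that would be reported as a differential effect of the intervention.

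Two lesser issues sit alongside. Work experience and work satisfaction are compared across different sets of counselors in the two arms. And interaction tests meant to check an assumption of no moderation are run in a trial sized for its main effect only.

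**Working it through.** **1. Does adherence meet the requirements of the model?**

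| Requirement | What the article gives |
|---|---|
| Fixed before allocation | Logs are written after each visit; the counselor is appointed after randomization |
| Same meaning in both arms | Happiness Route: five stages, one to four flexible sessions plus a booster. Customized Care: two visits to optimize care |
| Same measurement in both arms | Similar logs, shorter in control, with an added record of care changes |
| Not influenced by response | Happiness Route logs also hold motivation, progress and stage; whether these enter the score is not stated |

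The first two requirements fail on the text. The third fails in part. The fourth is open.

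**2. How large could a false signal be?** Assume a standardized score and outcome and 102 analyzed per arm. Let Δ be the adherence-outcome slope in the Happiness Route minus that in control. The standard error of Δ is about √(2/102) = 0.140, and the chance of a two-sided 0.05 significant interaction is about Φ(Δ/0.140 − 1.96).

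| Δ (assumed) | Δ/SE | Chance of significance |
|---|---|---|
| 0 | 0 | 5% (both tails) |
| 0.10 | 0.71 | 11% |
| 0.15 | 1.07 | 19% |
| 0.20 | 1.43 | 30% |
| 0.30 | 2.14 | 57% |

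Simulation of 4,000 trials per setting agrees: about 5% for equal correlations of 0.3, 11% for 0.3 against 0.2, 19% for 0.3 against 0.15, and 30% and 58% for 0.2 and 0.3 against zero. The article gives no value of Δ, so this shows dependence on Δ and is not an estimate for this trial.

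**3. Work experience and work satisfaction.** Counselors complete their questionnaire before starting study work, so participant response cannot feed back into these indices. But each counselor serves one arm, and the project leader chooses the counselor after allocation. Each interaction is thus a slope among one set of counselors minus a slope among another, and randomization of participants protects neither slope.

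**4. Stated sample size.** With d = 0.35, one-sided alpha 0.05 and 80% power, the normal approximation gives 101 per arm. The noncentral t gives power 0.798 at 101 and 0.801 at 102, so 102 reproduces. Then 102/0.8 = 127.5, rounded up to 128 per arm and 256 in total.

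**5. Interaction power at that size (scenarios).** For a binary moderator with share p at one level and change-score SD 1, SE = √[(4/N)(1/p + 1/(1 − p))] and power = Φ(δ/SE − 1.96).

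- N = 204, p = 0.5: SE = √(16/204) = 0.280. For δ = 0.35, 0.35/0.280 = 1.25 and power is 24%. For δ = 0.175, power is 9%.
- N = 256 (all randomized, imputed), p = 0.5, δ = 0.35: SE = 0.250, power 29%.
- N = 204, δ = 0.35: power 21% at a 30/70 split and 17% at 20/80. At 20/80 with δ = 0.175 it is 7%.
- If 0.35 is in raw SD units and the baseline to nine-month correlation is r, the change-score SD is √[2(1 − r)]. For r = 0.4 to 0.7 and δ = 0.35, power is 21% to 36% at N = 204 and 25% to 44% at N = 256.
- One-sided at 0.05, SD 1, even split, δ = 0.35: 35% (N = 204) and 40% (N = 256).
- For a standardized continuous index at N = 204, power is 24% at a slope difference of 0.175 per SD and 70% at 0.35 per SD.

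For 80% two-sided power at δ = 0.35 and p = 0.5, N = 16 × [(1.96 + 0.84)/0.35]² ≈ 1,026 analyzed.

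**The case against.** The strongest reply concerns what adherence means here. Table 1 lists it as adherence of counselors, which points to fidelity of delivery rather than participant attendance. The number of Happiness Route sessions varies by design, so fewer sessions is not lower adherence. Nothing says that logged progress enters the score, and a condensed article may leave the index to the full protocol. This stands as far as it goes: confounding by response is possible, not shown. It does not rescue the interaction, because fidelity of delivery also arises after allocation and still refers to two different programs.

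A reader might infer that false moderation is likely, at 30% to 57% or more. Those rates need a correlation of 0.2 or above in the Happiness Route and exactly zero in control, where logs are also kept. With equal correlations the rate is nominal. The planned end of the sessions at about three months, against an outcome at nine, also makes reverse influence less direct. The article supports neither zero in control nor any other value.

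A reader might also infer that null interactions will be reported as confirming no moderation. The article states an expectation and says it will be tested, but gives a rule only for significant results. Nor does it claim power for interactions, and low interaction power is usual in a trial sized for its main effect. These points confine the power issue to a secondary caution.

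Finally, the two log forms are described as similar, so measurement differs in part rather than wholly.

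**Conclusion.** The point holds for adherence. As written, the plan would read a significant adherence-by-condition interaction as a differential effect of the intervention, and the timing and content of the measure do not allow that reading. This conclusion needs no numerical assumption. How often a misleading result would occur cannot be stated, because it depends on an unreported difference in correlation between arms.

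The work experience and work satisfaction interactions can be estimated, but they are observational comparisons of different counselors.

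The power point is secondary. For binary-moderator interactions of half to all of the main effect, two-sided power is roughly 9% to 44% (7% at a 20/80 split with half the effect). The familiar 24% is one scenario in that range: even split, full 0.35 SD, 204 analyzed, SD 1. It is not a property of the plan, and it does not carry over directly to the continuous indices. The article does not say how a null result will be read, so the caution is against a possible reading, not a stated one.

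One of six moderator analyses is affected in substance, and the primary comparison is untouched.

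**What to change.** - Remove adherence from the condition-by-moderator regressions. Report it as an exploratory process analysis within each arm, chiefly the Happiness Route, and state which log items form the score and whether motivation, progress or stage are among them.
- Keep the work experience and work satisfaction interactions, labeled as non-randomized comparisons because counselors serve one arm only and are appointed after allocation.
- For every remaining moderator, report the interaction with its 95% confidence interval and state that a non-significant result will not be taken as support for equal benefit.

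The cost is a change of analysis wording, with no new data collection. One planned moderator becomes descriptive, and the moderator results can say less about whether benefit is uniform.

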### Power calculation and sample size

Based on a meta-analysis of previous studies in positive psychology, conducted with instruments that are similar to the MHC-SF
[27], we expect a small to medium effect size for the intervention Happiness Route (Cohen’s d = 0.35). A pilot study
[25] and experiences from previous practice showed that there are no negative effects on the well-being of participants. We therefore specified a one-tailed test with an alpha level of 0.05 under the assumption that the Happiness Route will be more effective than the Customized Care group, as the latter is not intended to improve positive mental health. This has also been shown in previous studies on positive psychological interventions
[27]. Given ethical considerations, Knottnerus and Bouter
[61] argued that one-sided testing is preferable under these circumstances. Power analysis with the program GPower with a power of 0.80 (1 – beta of 0.20), indicates that 102 participants are needed in each condition. We used a maximal drop-out rate of 20% which is a conservative estimate from previous experience. In everyday practice, the drop-out was about 10% of the more than 500 people who already participated in a Happiness Route. With a maximal drop-out of 20%, we need 128 participants in each condition, 256 in total.

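### The 0.80 power was worked out for a one-tailed comparison, but effectiveness is to be judged by a repeated-measures MANOVA for which that figure is not supported

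*Protocol article*

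**What the plan says.** Under the heading on power calculation and sample size, the protocol article takes d = 0.35 from a meta-analysis and continues: "We therefore specified a one-tailed test with an alpha level of 0.05". The result is given as follows: "Power analysis with the program GPower with a power of 0.80 (1 – beta of 0.20), indicates that 102 participants are needed in each condition". After an allowance for 20% drop-out, "we need 128 participants in each condition, 256 in total". The type of test is not named beyond its being one-tailed.

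Under the heading on multivariate analyses, the article says: "We will use MANOVA analyses to assess the effectiveness of the intervention in reaching its primary and secondary outcomes". It adds: "The measures at baseline, post-treatment, and follow-up are repeated measures and the experimental condition versus the control condition is the independent variable". That section gives no sidedness and no correlation between occasions. It does not say which MANOVA effect (condition, or condition by time) decides the primary hypothesis, and it names no primary time point. Cohen's d is to be reported at both post-intervention and follow-up. A single change score (nine months minus baseline) appears only in the moderator models.

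**The concern.** A sample size carries its power only for the test it was computed for. Here the sizing test is one-tailed and compares two groups on one quantity. The deciding analysis spans three occasions. With two groups and three occasions, the condition-by-time effect has 2 degrees of freedom, and a multivariate F test with more than one degree of freedom cannot be one-tailed.

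Two things are at stake. First, readers are told that the trial has an 80% chance of detecting d = 0.35, and nothing in the article shows this for the analysis that will be run. Second, with two different tests in the same article, a borderline result could count as positive under the one-tailed rule of the sample-size section and as negative under the F test of the analysis section.

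**Working it through.** **Inputs from the article.** d = 0.35; alpha 0.05, one-tailed; power 0.80; equal allocation; drop-out 20%; three measurement occasions. **Assumed, because the article gives none:** an equal correlation ρ between all pairs of occasions (range 0.3 to 0.7), equal variances, and, for the baseline-adjusted test, a correlation r between baseline and outcome. Clustering is ignored throughout.

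**1. The article's own figure.** For a two-group t-test the noncentrality is d·√(n/2), with 2n − 2 degrees of freedom. At n = 102 this is 0.35 × √51 = 2.50 on 202 df. One-tailed power at 0.05 is 0.801 (0.798 at n = 101), so 102 is reproduced. Drop-out: 102 / 0.80 = 127.5, rounded up to 128 per arm and 256 in total. That the sizing test was a t-test is inferred from this match.

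**2. Loss of direction only.** The same comparison, two-sided at 0.05 with 102 per arm, has power 0.701. Reaching 0.80 takes 130 analysed per arm, or 130 / 0.80 = 162.5, so 163 per arm and 326 in total.

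**3. Condition-by-time test, 2 df.** With equal correlations, the two change scores from baseline have covariance matrix (1 − ρ) × [[2, 1], [1, 2]] in SD units. The noncentrality is (n/2) × δ′Σ⁻¹δ, which reduces to:

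- effect d at both follow-ups: λ = n·d² / [3(1 − ρ)]
- effect d at one follow-up and d/2 at the other: λ = n·d² / [4(1 − ρ)]

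Here n·d² = 102 × 0.1225 = 12.495. At ρ = 0.5, for example, λ = 12.495 / 1.5 = 8.33 (sustained) and 12.495 / 2 = 6.25 (halved). The reference distribution is F with 2 and 201 df, with a critical value of 3.04.

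| Assumed ρ | λ, sustained | Power, sustained | λ, halved at one | Power, halved at one |
|---|---|---|---|---|
| 0.3 | 5.95 | 0.57 | 4.46 | 0.45 |
| 0.4 | 6.94 | 0.64 | 5.21 | 0.51 |
| 0.5 | 8.33 | 0.73 | 6.25 | 0.60 |
| 0.6 | 10.41 | 0.83 | 7.81 | 0.70 |
| 0.7 | 13.88 | 0.92 | 10.41 | 0.83 |

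With a sustained effect, power passes 0.80 between ρ = 0.5 and ρ = 0.6.

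**4. If the condition main effect were meant instead.** Averaged over all three occasions, with no difference at baseline and d = 0.35 afterwards, the two-sided 1-df test has power 0.62 at ρ = 0.3 and 0.46 at ρ = 0.7. Power here falls as the correlation rises, so the unstated choice of effect matters.

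**5. A single contrast adjusted for baseline.** Adjustment turns d into d / √(1 − r²). For r = 0.4, 0.5 and 0.6 this is 0.382, 0.404 and 0.438. With 102 per arm, two-sided power at 0.05 is 0.77, 0.82 and 0.87, against 0.70 unadjusted. One-sided at 0.05 it is 0.86, 0.89 and 0.93, against 0.80 unadjusted.

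**The case against.** The strongest reply is that the repeated-measures test makes use of the baseline, so it may have more power than the test used for sizing. That stands: at ρ = 0.6 or above with a sustained effect, the 2-df test exceeds 0.80. In addition, 102 per arm is the article's own worst case. Drop-out in everyday practice is put at about 10%, which would leave 128 × 0.90 = 115 per arm; the sustained-effect power is then 0.78 at ρ = 0.5 and 0.87 at ρ = 0.6. A reader might therefore infer from the mismatch that the trial is underpowered, and the documents do not support that. They give no correlation and no expected course of the effect over time, so a shortfall is possible but not shown.

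A second reply is that the exact contrast is detail that an analysis plan would supply. This has some force: a 1-df contrast tested at two-sided 0.10 with the direction checked would keep the 0.801. But the article does not leave the matter open. It states both a sizing test and a deciding analysis, and the two differ.

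Third, a one-sided test that is declared and argued in advance is not an error. The article also rests its choice on a meta-analysis and a methodological source that cannot be judged here. A reader might set the description of Customized Care as the best possible care against the statement that it is not meant to improve positive mental health. These do not conflict, since optimising care in a problem-focused way and raising positive mental health are different aims. Nor is a result favouring Customized Care ruled out by the plan, because the F test would detect a difference in either direction.

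Finally, a reader might suppose that the MANOVA takes the three MHC-SF subscales as joint outcomes. The analysis section describes repeated occasions, not subscales, and the article names positive mental health, measured by the MHC-SF, as the primary outcome. No power figure for a subscale analysis belongs here.

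**Conclusion.** The point holds as a mismatch between the test used for sizing and the analysis planned for the primary hypothesis. The figure of 102 per condition is correct for a one-tailed two-group comparison, and the article gives no basis for carrying its 0.80 over to the MANOVA. Loss of direction by itself costs about 10 percentage points (0.801 to 0.701). For the 2-df test the range is wide and lies on both sides of 0.80. These ranges rest on d = 0.35, 102 analysed per arm, equal correlations and variances across occasions, and no clustering. Multiple imputation of all 256 participants does not settle the matter, because it does not restore the information lost to drop-out. The right conclusion is that the stated power is unsupported for the planned analysis, not that the trial has been shown to miss it.

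**What to change.** Name one primary test and use it in both sections: a single-df contrast between conditions on the MHC-SF total at one named time point, adjusted for baseline MHC-SF, with its sidedness stated. Keep N = 256 and restate the power for that test with the assumed baseline correlation, using the figures in step 5 of the working; then show the effect of clustering. If the sponsor keeps one-sided 0.05, the existing 0.80 stands without adjustment, provided the analysis section also says that the primary test is one-sided. Keep the repeated-measures MANOVA as a supportive analysis and say which of its effects is of interest.

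If the MANOVA is to remain primary, the alternative is to redo the power calculation for its named effect, with a stated between-occasion correlation and a stated pattern of effect over time.

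The cost is rewording two sections. No participants are added. If a two-sided test is chosen, the declared power is below 0.80 unless the baseline correlation is about 0.5 or higher.
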